## Abstract

**Background:**

The National Chest Pain Center Accreditation Program (CHANGE) is the first hospital-based, multifaceted, nationwide quality improvement (QI) initiative, to monitor and improve the quality of the ST segment elevation myocardial infarction (STEMI) care in China. The QI initiatives, as implementation strategies, include a bundle of evidence-based interventions adapted for implementation in China. During the pandemic of coronavirus disease 2019 (COVID-19), fear of infection with severe acute respiratory syndrome coronavirus 2, national lockdowns, and altered health care priorities have highlighted the program’s importance in improving STEMI care quality. This study aims to minimize the adverse impact of the COVID-19 pandemic on the quality of STEMI care, by developing interventions that optimize the QI initiatives, implementing and evaluating the optimized QI initiatives, and developing scale-up activities of the optimized QI initiatives in response to COVID-19 and other public health emergencies.

**Methods:**

A stepped wedge cluster randomized control trial will be conducted in three selected cities of China: Wuhan, Suzhou, and Shenzhen. Two districts have been randomly selected in each city, yielding a total of 24 registered hospitals. This study will conduct a rollout in these hospitals every 3 months. The 24 hospitals will be randomly assigned to four clusters, and each cluster will commence the intervention (optimized QI initiatives) at one of the four steps. We will conduct hospital-based assessments, questionnaire surveys among health care providers, community-based household surveys, and key informant interviews during the trial. All outcome measures will be organized using the RE-AIM (reach, effectiveness, adoption, implementation, maintenance) framework, including implementation outcomes, service outcomes (e.g., treatment time), and patient outcomes (e.g., in-hospital mortality and 1-year complication). The Consolidated Framework for Implementation Research framework will be used to identify factors that influence implementation of the optimized QI interventions.

**Discussion:**

The study findings could be translated into a systematic solution to implementing QI initiatives in response to COVID-19 and future potential major public health emergencies. Such actionable knowledge is critical for implementors of scale-up activities in low- and middle-income settings.

**Trial registration:**

ChiCTR 2100043319. Registered on 10 February 2021

**Supplementary Information:**

The online version contains supplementary material available at 10.1186/s13012-021-01107-1.

Contributions to the literature
This study will be the first to identify multilevel factors that emerge within the context of COVID-19 and influence implementation of the interventions to improve the quality of care for acute cardiac events. The findings will provide implications for where adjustments to the interventions could be made in response to COVID-19 and other potential pandemics or health emergencies.This study will provide a novel model to measure complex interventions in real-world health care system settings, including measures of clinical effectiveness and implementation strategies for quality improvement initiatives of acute cardiac care, by using a stepped wedge cluster randomized control design, under a modified RE-AIM (reach, effectiveness, adoption, implementation, maintenance) framework.The outcomes of this study will generate actionable knowledge about process outcomes and feasibility, including core components that are transferrable, and where local adaptation is needed for scale-up activities in low- and middle-income settings, to improve quality of care for acute cardiac events in response to COVID-19 and other potential pandemics or health emergencies.

## Background

The coronavirus disease 2019 (COVID-19) pandemic requires enormous deployment of health care resources worldwide. Fear of infection with severe acute respiratory syndrome coronavirus 2 (SARS-CoV-2), national lockdowns, and altered health care priorities can compromise the quality of care for non-COVID-19 diseases. The downstream effects have been observed in the acute care sector, which has been oriented toward a “war footing” for COVID-19 through major reorganization of emergency care facilities. This is particularly true for China and other low- and middle-income countries, where financial, technical, and staff resources are limited.

Importance of improving quality of care for acute cardiac events in China

ST segment elevation myocardial infarction (STEMI) is the deadliest and most time-sensitive acute cardiac event. Poor quality of care for patients with STEMI contributes to increased mortality from cardiovascular diseases, which is the leading cause of death in China. STEMI cases require rapid coordination of care beginning at the time of symptom onset. Percutaneous coronary intervention (PCI) within 120 minutes from onset is the typically recommended treatment, according to American College of Cardiology/American Heart Association (ACC/AHA) guidelines [1]. Despite the widespread promulgation and endorsement of these guidelines and the strong evidence base underpinning many guideline recommendations, their translation into clinical practice remains suboptimal [2, 3]. On the basis of our prior study, the time from onset to PCI is approximately 291 minutes in China, and only 7% of patients receive timely PCI therapy. Therefore, reducing the treatment delay by organizing delivery of care on a regional basis is a priority for improving quality of STEMI care in China.

The Chinese Cardiovascular Association launched the National Chest Pain Center Accreditation Program (CHANGE) in January 2016. This is the first nationwide, hospital-based, multifaceted, continuous quality improvement (QI) initiative, with aims to monitor and improve the quality of care for acute cardiac events (ClinicalTrials.gov, NCT04014972). The QI initiatives, as implementation strategies, include a bundle of evidence-based interventions adapted for implementation in China. These are in line with global best practices: (i) accreditation of hospital-based chest pain centers (CPCs), (ii) establishing a unified data registry for quality monitoring and assessment, and (iii) providing ongoing quality review and feedback. The operational structure was developed at the start of the program (Appendix Figure 1). The program is made available to all secondary and tertiary hospitals, and hospitals continue to join the program in a staggered manner. With the support of the National Health Commission (NHC), based on the CPC Accreditation Criteria issued by the Chinese Society of Cardiology, the CHANGE program has implemented the accreditation and development of CPCs (Appendix Figure 2). The CHANGE program developed the China CPC Data Reporting Platform, a web-based, unified national database serving as a national surveillance system for monitoring, evaluation, and feedback regarding quality of care for reported STEMI events (Appendix Table 1). As of June 30, 2019, there were 2,885 hospitals across 31 provinces of China and a total of 463,827 patients with a STEMI diagnosis enrolled in the program. Our preliminary analysis using baseline and quarterly data during January 2016 and June 2019 demonstrated that the QI initiatives can shorten onset to reperfusion times and subsequently reduce in-hospital mortality.

Challenges to quality improvement initiatives in response to COVID-19

The COVID-19 pandemic is challenging population health and health care systems in unprecedented ways, and the effects will last for decades to come [4]. Most countries have implemented stringent infection-control measures, including but not limited to social distancing measures, emergency infection protocols instituted in hospitals to contain COVID-19, and adjustment of clinical services. The response to COVID-19 can compromise rapid triage and may impact optimal treatment delivery for patients with acute cardiac events. Several studies have reported substantial declines in the number of patients presenting with acute cardiac events as well as the number of emergency coronary procedures, in both high-income and low- and middle-income countries [5–7]. Preliminary available data from the CHANGE program show that hospital admissions among patients with STEMI decreased by more than 50% in February 2020 compared with the same period in 2019. The time from onset to PCI increased from 237 minutes in February 2019 to 342 minutes in February 2020.

There are two major public health concerns with respect to the care in STEMI and other acute cardiac events: (i) delays in presentation, and (ii) delays in treatment [8–13]. First, causes for late presentation for STEMI are likely multifactorial and may include patient fear of contracting an infection from within the health care system. The lack of knowledge compounded by fear of the SARS-CoV-2 make patients with STEMI much less likely to seek help. The emphasis on social distancing might have inappropriately convinced patients to avoid in-person health care. Proper education including STEMI awareness and COVID-19 knowledge is warranted during a pandemic [8, 9, 14]. In the CHANGE program, accredited CPCs in hospitals should follow the criteria for establishing a medical consortium of STEMI care. Hospitals should be partnered with community health centers to form an information-sharing and resource-management model. Health workers at community health centers conduct health management of STEMI patients and health education among community residents, which are part of the essential public health services in China. Thus, community-based education supervised by hospitals within a medical consortium should be established within routine services delivery, to inform the public that the CPCs remain fully operational and have stringent infection-control protocols in place during the pandemic.

Second, delays in treatment may be prolonged because the emergency infection protocols (e.g., COVID-19 screening after hospital arrival) could result in a considerable delay in timely treatment. Additionally, care providers may be subject to travel restrictions or be dispatched to the front lines in fight against COVID-19, leading to a shortage of health workers and systemic overload. For example, over 40,000 medical professionals from other parts of China have been sent to Wuhan, Hubei Province, the epicenter of the outbreak, thereby draining the available resources for other disease conditions. Stresses on health systems are also likely to affect critical supply chains for essential medicines and equipment. Thus, it is imperative to improve the health care system’s ability to maintain care coordination for operational integrity with respect to patients with STEMI. A balance must be struck between identifying appropriate patients for PCI intervention for STEMI, regardless of their COVID-19 status, and maintaining the safety of health care workers who may be exposed to the virus as well as minimizing contamination of cardiac catheterization laboratory facilities [15, 16]. Prior studies have shown that a dedicated regional coordinator in charge of implementing systematic improvements within hospitals and EMS agencies in the region could play a critical role in maintaining coordination of care [17].

It is therefore necessary that health care systems develop plans for optimizing the existing QI initiatives, to mitigate the negative impact of the COVID-19 outbreak and to protect patients with acute cardiac events from nosocomial infection and limited access to care. This is not simply a problem limited to a single specialty or condition but rather a problem that holds lessons in acute illness care.

Contributions to current theory practice and policy

Following the positive preliminary phase and considering the needs in response to COVID-19, the QI initiatives should be optimized, as recommended by the NHC [18]. In collaboration with NHC partners and CHANGE program staff, this study will design an updated implementation strategy for this optimization, to enhance the adoption, implementation, and sustainability of QI initiatives in the context of COVID-19. However, little is known regarding identification of the best policy options and solutions based on China’s real-world situations, to improve the quality of care in response to COVID-19. Furthermore, to our knowledge, no studies have focused on implementation strategies to provide generalizable data that can inform replication and scale-up activities [17, 19]. Therefore, this study will add evidence-based interventions to current QI initiatives, to develop optimized QI initiatives from a multidisciplinary research perspective. The main contributions of the proposed project include the following.

First, a Consolidated Framework for Implementation Research (CFIR) framework will be used to identify multilevel factors that emerge within the context of COVID-19 and influence implementation of the current QI interventions [20], and where adjustments and refinements to the intervention could be made in response to COVID-19.

Second, a novel model will be used to measure the implementation strategy of the optimized QI initiatives, using a stepped wedge cluster randomized control design, under a modified RE-AIM (reach, effectiveness, adoption, implementation, maintenance) framework [21]. The RE-AIM model is a practical tool that assesses complex interventions in real-world health care system settings, including measures of clinical effectiveness and implementation strategies. The stepped wedge design will provide more generalizable estimates than traditional study designs because it allows for regular data analysis and iterative dissemination of results—internally, to support programmatic improvements and with partners for embedded research practices.

Third, the outcomes of this study could be translated into a systematic solution for implementing the QI initiatives in response to COVID-19 and other potential pandemics or health emergencies. The synthesis of the CFIR framework and RE-AIM evaluation framework will enhance the traditional stepped wedge design by including measures of implementation fidelity, and will generate knowledge about process outcomes and feasibility including barriers and facilitators, core components that are transferrable, and where local adaptation is needed for replication in other settings [22]. This actionable knowledge is a critical need for implementors of scale-up activities in low- and middle-income settings.

## Methods

### Study aims

The overall goal is to minimize the untoward impact of the evolving COVID-19 outbreak on the quality of STEMI care by optimizing the implementation of QI initiatives. The specific objectives of the study include the following:
To develop hospital-based interventions that optimize the QI initiatives, adapted to China’s health care system.To implement the optimized QI initiatives, and evaluate the clinical effectiveness and implementation strategy using measures of reach, adoption, implementation, and maintenance.To develop strategic options in scale-up activities for the optimized QI initiatives under two scenarios, including the outbreak stage of a major public health emergency and the pandemic period.

### Study design

The theoretical model for this study is a synthesis of implementation and evaluation of the optimized QI initiatives under the theory of implementation science (Fig. 1). The RE-AIM framework will be used to evaluate the implementation strategy, in which three dimensions of outcomes will be included, namely implementation outcome, service outcome, and patient outcome. Effectiveness is measured according to service outcome and patient outcome. Reach, adoption, implementation, and maintenance are measured according to implementation outcomes. The CFIR framework will be used to identify the barriers and facilitators influencing the implementation strategy. Based on the theoretical model, we will use a stepped wedge cluster randomized control design to evaluate the implementation and effectiveness of the optimized quality improvement initiatives (Fig. 2).

**Fig. 1 Fig1:**
[figure not shown]
Theoretical model for the study

**Fig. 2 Fig2:**
[figure not shown]
Study flow diagram

### Setting and facility selection

The study will be conducted in cities of Wuhan, Suzhou, and Shenzhen of China. Study sites are selected by the NHC partners and the CHANGE program staff based on region, population size, economic level, traffic conditions, and representativeness of the prehospital model. The prehospital model varies across cities. In general, there are now at least three prehospital models delivering emergency medical services (EMS). The first type operates independently (e.g., Wuhan), the second is under the authority of emergency centers (e.g., Suzhou), and the third is delivered by the emergency department of hospitals (e.g., Shenzhen). Two districts will be randomly selected in each of the three cities. All hospitals registered in the CHANGE program in the six selected districts will be included; finally, this study will include 24 registered hospitals.

### Intervention

The intervention will be applied at the hospital level. Intervention hospitals will carry out the optimized QI initiatives, and hospitals that have not been enrolled in the intervention will conduct the current QI initiatives (Table 1). In terms of the current QI initiatives, hospitals need to go through the accreditation process to develop an accredited CPC. Accredited CPCs should follow the criteria for improving the quality of care of patients with STEMI [23]. The continuous QI activities require hospitals to report real-time clinical data for monitoring the CPC performance. Improvement in adherence to the guideline recommendations is facilitated through monthly, quarterly, and annually hospital-specific performance feedback reports [24]. The hospital-specific data are compared against a variety of internal and external benchmarks, including the temporal trend in performance and comparison points to regional or national performance thresholds [25]. In terms of the two added interventions among the optimized QI initiatives, the dedicated regional coordinator will be charged with coordinated care between community, hospitals, and EMS agency [26]. The training outreach targeting healthcare professionals will be conducted by hospitals, and the education targeting community residents will be conducted by community health centers [27].

**Table 1 Tab1:** Optimized and current QI initiatives in the CHANGE program

QI initiatives	Details	Classification
(1) Accreditation of hospital-based CPCs	▪ The comprehensive center criteria are applicable to the comprehensive CPCs at tertiary hospitals; while the basic center criteria targets the basic CPCs at secondary hospitals. ▪ Both editions of the criteria include 5 dimensions of qualification: conditions of facilities, diagnosis and treatment process, integration of prehospital and hospital care, training and education, and real-time data reporting. ▪ Registered hospitals need to go through 3 stages including self-assessment, accreditation, and re-accreditation every 3 years, to develop an accredited CPC. ▪ The accreditation process is jointly led by the China CPC Headquarters, Regional Accreditation Offices, and Provincial-level CPC Alliances.	Current and optimized
(2) Quality monitor and assessment	▪ Accredited hospitals should continuously report data for monitoring and feedback. ▪ The indicators for measuring the CPC performance in the quarterly and annually benchmarked reports are developed by the China CPC Headquarters, based on the ACC/AHA Performance Measures and clinical practice guidelines. ▪ There are two sets of performance measures respectively for comprehensive and basic CPCs. ▪ Ranking of a CPC is calculated based on the percentile of each indicator and a weighted composite score. The score of 100, 80, 60, 40, 20, and 0 are for ranking the top 10%, 10–30%, 30–50%, 50–70%, 70–90%, and 90–100% of the measure among the entire accredited CPCs.	Current and optimized
(3) Quality review and feedback	▪ Improvement in adherence to the guideline recommendations is facilitated through monthly and quarterly hospital-specific performance feedback reports. ▪ The hospital-specific data are compared against a variety of internal and external benchmarks, including the temporal trend in performance and comparison points to regional or national performance thresholds. ▪ A series of regular meeting, QI analysis meeting, and case study meeting are carried out at least once every quarter for sharing of ‘best practice’ clinical support tools.	Current and optimized
(4) Dedicated regional coordinator	▪ Dedicated regional coordinator charged with implementing systematic improvements within every hospital and EMS agency will be assigned by city-level CPC Alliances. ▪ Dedicated regional coordinators will work with the local health bureau to promote the optimized QI initiatives. ▪ The work of dedicated regional coordinators will include synthesizing emergency infection protocols to contain COVID-19 with QI initiatives, coordinating care between community, hospitals, and EMS agency, maintaining the safety of healthcare workers, minimizing contamination of laboratory facilities. ▪ The work of dedicated regional coordinators will be supervised by the city-level CPC Alliances and the China CPC Headquarters.	Optimized
(5) Education and training activities	▪ The training on emergency infection protocols instituted in hospitals to contain COVID-19 targeting at healthcare professionals will be conducted by hospitals ▪ Education on STEMI awareness and COVID-19 knowledge targeting community residents will be conducted by community health centers, which are trained and supervised by hospitals within the medical consortium.	Optimized

*QI* Quality improvement; *CHANGE* National Chest Pain Center Accreditation Program; *CPC* Chest pain center; *EMS* Emergency medical services; *ACC/AHA* American College of Cardiology/American Heart Association; *COVID-19* Coronavirus disease 2019; *STEMI* ST segment elevation myocardial infarction

Sampling

In this study, we will conduct a rollout to registered hospitals every 3 months, which will be based on the pilot experience, local contextual factors, budgetary and feasibility considerations. Patients with STEMI in registered hospitals will be consecutively enrolled in five 3-month steps. No intervention will be applied in the first step among all registered hospitals. Hospitals will be randomly allocated to one of four clusters, with six hospitals in each cluster. Each cluster will commence the intervention at one of the four remaining steps. All hospitals will be on the intervention in the final step. Characteristics of hospitals with STEMI cases enrolled during January and June 2020 are shown in Table 2, by district (Table 2).

**Table 2 Tab2:** Characteristics of sample hospitals, by district

City	District	Population	Land area (km^2^)	Number of hospitals	STEMI patients	In-hospital mortality
Wuhan	Jianghan	496,289	28.3	3	459	1.53
	Qiaoko	528,604	40.1	4	319	3.13
Suzhou	Gusu	957,500	83.4	4	167	3.86
	Kunshan	1,665,900	931.5	6	157	1.27
Shenzhen	Futian	1,633,700	78.5	4	250	6.00
	Luohu	1,039,900	78.7	3	229	4.37

*STEMI* ST segment elevation myocardial infarction

### Randomization

Randomization will be done centrally among all 24 hospitals before initiating the intervention in the first-cluster hospitals. The allocation codes will be concealed by the statistician separately and will be provided to CHANGE program staff who are responsible for initiation of the intervention. The cluster order for implementation at each step will be determined randomly by an external technical advisor using a random number generator. Randomization will occur 6 months prior to rollout of the intervention in the next cluster. This will enable blinding to the random order of clusters for the NHC partners and CHANGE program staff involved in implementation while also allowing for an annual 6-month planning stage prior to starting the intervention.

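### The Randomization section gives conflicting timings; under either, the full cluster order is settled by the first crossover, so the claimed staff blinding cannot be relied on from then on

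*Protocol article*

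**What the plan says.** All statements are in the protocol article. The term cluster there means a group of six hospitals that crosses over together, which is a sequence in usual stepped wedge language.

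- **Timing, one draw** (Randomization): "Randomization will be done centrally among all 24 hospitals before initiating the intervention in the first-cluster hospitals".
- **Timing, rolling draw** (Randomization): "Randomization will occur 6 months prior to rollout of the intervention in the next cluster". The order is worded step by step: "The cluster order for implementation at each step will be determined randomly by an external technical advisor using a random number generator".
- **Who gets the codes** (Randomization): the statistician conceals the allocation codes, which "will be provided to CHANGE program staff who are responsible for initiation of the intervention".
- **Who is blinded** (Randomization): "This will enable blinding to the random order of clusters for the NHC partners and CHANGE program staff involved in implementation".
- **Planning** (Randomization): the timing is justified as "while also allowing for an annual 6-month planning stage prior to starting the intervention".
- **Step length** (Intervention, sampling paragraph): "we will conduct a rollout to registered hospitals every 3 months" and "Patients with STEMI in registered hospitals will be consecutively enrolled in five 3-month steps". The first step has no intervention anywhere, and one of the four clusters starts at each remaining step.
- **Allocation** (same paragraph): hospitals go at random into four clusters of six. The article neither states nor excludes stratification or another restriction.

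**The concern.** The section asserts a property, blinding to the order, and gives a schedule that should produce it. The schedule is stated in two ways that do not agree, and the lead time is twice the step length. A lead of two steps in a design with only four sequences uses up the uncertainty about the order very early.

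This matters because concealment of the order is what protects the control quarters. Table 1 has hospitals reporting their own data and being ranked on them. Strengths and limitations says that all registered hospitals strongly prefer to receive the intervention. A team that knows it is next, or next but one, has both reason and opportunity to start parts of the package early or to change its reporting while it still counts as control. Early starting would pull the estimated effect towards zero. Later readers would also credit the trial with a safeguard that its own timetable may not deliver.

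**Working it through.** **Inputs.** Five 3-month steps, the first all control, four clusters, a 6-month lead (Randomization; Intervention). City counts from Table 2: Wuhan 3 + 4 = 7, Suzhou 4 + 6 = 10, Shenzhen 4 + 3 = 7, total 24.

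**1. Calendar.** Let month 0 be the start of step 1. The trial runs 5 × 3 = 15 months. Cluster k starts at month 3k. Under the rolling rule it is drawn at month 3k − 6.

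| Cluster | Drawn | Starts | Planning window |
|---|---|---|---|
| 1 | −3 | 3 | −3 to 3 |
| 2 | 0 | 6 | 0 to 6 |
| 3 | 3 | 9 | 3 to 9 |
| 4 | 6 | 12 | 6 to 12 |

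The windows begin every 3 months and overlap. That is workable, but none of them is annual.

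**2. When the order is settled.**
- One-off draw: before month 3, by its own wording.
- Rolling draw: one cluster is drawn from month −3, two from month 0 and three from month 3. With four clusters, three draws determine the fourth. The order is complete at month 3, the moment of the first crossover.
- Two-stage reading (hospitals into clusters once, cluster order drawn step by step): the order follows the rolling column, so again month 3.

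**3. How much control time is exposed.** Control cluster-quarters by step: 4 + 3 + 2 + 1 + 0 = 10. Those after month 3: 3 + 2 + 1 = 6. So 6 of 10 run after the full order is settled.

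If each draw is disclosed when made, the control quarters during which a cluster's own start is known are:
- cluster 1, months 0–3: 1
- cluster 2, months 0–6: 2
- cluster 3, months 3–9: 2
- cluster 4, months 3–12, by elimination: 3

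The total is 8 of 10. Only clusters 3 and 4 in step 1 remain uncertain.

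For comparison, a notice of one step (releases at months 0, 3 and 6, with cluster 4 then known by elimination) gives 1 + 1 + 1 + 2 = 5 of 10.

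**4. Who is blinded.** Program staff who initiate the intervention receive the codes. Program staff involved in implementation are blinded. The text does not say how these groups differ or when codes are released.

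**5. City spread, if the draw is unrestricted.** For one sequence of six from 24, the chance of no hospital from a given city is:
- Wuhan or Shenzhen: C(17,6)/C(24,6) = 12,376/134,596 = 0.092 each
- Suzhou: C(14,6)/C(24,6) = 3,003/134,596 = 0.022

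The expected number of missing city-sequence pairs is 4 × (0.092 + 0.022 + 0.092) = 0.82. Simulating 100,000 allocations of 7/10/7 hospitals into four groups of six gives a probability of 0.584 that at least one sequence lacks a city. This uses only the hospital counts.

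**The case against.** **The timings may be reconcilable.** Hospitals could be grouped once and the order of groups drawn later. That is a fair reading, and it softens the conflict, but the text does not say it. It also leaves month 3 as the point where the order is complete, and it leaves the annual planning stage unexplained.

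**Drawn is not the same as disclosed.** This stands in part. The codes are said to be concealed and no release date is given, so a list could be held back after it is drawn. But the 6-month lead is justified as planning time, and nobody can plan for a cluster without being told which it is. The section cannot claim both benefits for the same people.

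**Code recipients may be a subset of program staff.** Possible. In that case the blinding sentence needs to name the others.

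**Early starting is conjecture.** No statement in the article shows it will happen, and the coordinators have to be assigned by city-level alliances, which limits it. The harm is therefore a risk of unknown size.

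**Stronger readings that the documents do not support.** A reader might infer that blinding is absent throughout. Rolling draws do conceal part of the order before month 3. A reader might also infer that a simple draw is specified and that cities and hospital volumes are left unbalanced. The article says only that allocation is random, and a condensed article may leave restriction to the full protocol. Imbalance is a chance event, not a stated feature. Nor can a precision gain from balancing be read off the documents: it would depend on assumed city-by-quarter shocks, and Statistical methods already plans an adjustment for pandemic severity.

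**Conclusion.** The section is wrong as written. It gives two randomisation timings that do not agree and a planning stage called annual in a 15-month trial. Under either timing the order is fully settled by the first crossover at month 3, with 6 of 10 control cluster-quarters still to come.

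That the blinding of partners and program staff fails from that point rests on one assumption: draws are disclosed to those who plan, which is the stated purpose of the lead. The sentence that gives codes to program staff conflicts with the blinding claim unless two groups of staff are meant.

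On balance, the supportable statement is conditional. No restriction is stated; if none exists, about 58% of allocations leave a sequence without one of the three cities.

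The change is worth making, since it corrects a stated safeguard at little cost. The size of any resulting bias cannot be derived from the documents.

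**What to change.** Replace the section by one procedure:

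1. One central draw before step 1 assigns all 24 hospitals to the four sequences and fixes their order.
2. The external advisor holds the list and releases each sequence at one stated notice period, the same for all and as short as planning allows.
3. Delete the word annual and the rule of randomising before each next cluster.
4. Limit the blinding claim to people who do not receive codes before release, and say who they are. Acknowledge that the last sequence becomes known by elimination once the third is released.
5. If the full protocol has no balancing rule, restrict the same draw so that each city appears in all four sequences. The counts 7, 10 and 7 do not divide by four, but a near-even spread exists, for example Wuhan 2/2/2/1, Suzhou 2/2/3/3 and Shenzhen 2/2/1/2, six per sequence. If the full protocol does have a rule, state it in one sentence.

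The cost is protocol wording and a short randomisation program. The real downside is a shorter planning lead for each cluster, so the notice period should be agreed with those who run the rollout.
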